### Sample size

Using the DASH [14] as the primary outcome measure, where a difference of 15 points is considered to be a clinically important difference [16] and using a between-group standard deviation of 22 points [18] a total of 51 patients would be needed in each group for a power of 90%. Allowing for a 20% loss to follow-up a total of 128 patients need to be randomized. Based on current surgery rates in the five participating centres and assuming a consent rate of 40–50% of those patients invited to take part we anticipate that the target sample size can be recruited within 16 months.

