**Methods/Design:**

A multi-centre, pragmatic, randomized, controlled trial is being conducted to evaluate the effect of static night splinting for six months on hand function, range of movement, patient satisfaction and recurrence at 1 year after fasciectomy or dermofasciectomy. Using a centrally administered computer randomization system consented patients will be allocated to one of two groups: i) splint group who will be given a static splint at approximately 10 to 14 days after surgery to be worn for 6 months at night time only as well as hand therapy; ii) non-splint group, who will receive hand therapy only. The primary outcome measure is the patient-reported Disabilities of the Arm, Hand and Shoulder Questionnaire (DASH). Secondary outcomes are total active flexion and extension of fingers, patient satisfaction and recurrence of contracture. Outcome measures will be collected prior to surgery, 3 months, 6 months and 1 year after surgery. Using the DASH as the primary outcome measure, where a difference of 15 points is considered to be a clinically important difference a total of 51 patients will be needed in each group for a power of 90%. An intention-to-treat analysis will be used.

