### Randomization

Patients will be randomized into one of two groups. One group will receive post-operative hand therapy only and the other group will receive hand therapy and a static night splint to be worn for 6 months. Randomization will be stratified by recruiting hospital (5 centres) and surgical procedure (dermofasciectomy or fasciectomy) in block lengths of 4.

Patients are randomized after surgery. This will ensure operating surgeons are unaware of group allocation at the time of surgery. A telephone based central computerised randomization service will be used to generate the allocation sequence and the treating hand therapists will obtain the group allocation just before or at the first post-operative hand therapy appointment by ringing a dedicated telephone number available 24 hours. Neither the patients nor the treating hand therapists can be blinded to group allocation.

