### Outcomes

Surgical release of a Dupuytren's contracture is primarily designed to 'open up' the palm and restore finger extensibility and improve hand function. Past studies of splinting have reported outcomes in terms of total active extension and total active flexion as well as self-reported symptoms, function and disability.

The primary outcome measure is self-reported hand function and disability assessed by the Disabilities of Arm Shoulder and Hand Questionnaire (DASH)[14]. The DASH is a 30-item patient-reported questionnaire designed to measure, symptoms and physical function in patients with musculoskeletal disorders of the upper extremity. There is no disease-specific outcome instrument for Dupuytren's contracture and the validation of the DASH has been done on a wide range of patients including Dupuytren's contracture. Longitudinal construct validity has been assessed in patients including those with DC and the responsiveness assessed by effect size is moderate (ES = 0.5). It has good concurrent validity with the subscales of the SF-36 [15] and test-retest reliability has been found to be excellent (ICC = 0.96) [16].

Secondary outcomes are range of movement, patient satisfaction and recurrence. Range of movement for digits I to IV will be assessed using a Rolyan hyperextension finger goniometer and following a standardised protocol. Total active flexion (TAF) and total active extension (TAE) will be recorded by adding individual DIP, PIP and MCP joint scores. Intra-tester reliability of finger goniometry using a standardised protocol has been shown as acceptable [17] with a within-tester error of less than 5 degrees.

Patient satisfaction will be assessed at 6 and 12 months using an 11 point verbal rating scale (VRS) with the question: How satisfied are you with the overall result of the surgery now? A score of 0 means completely dissatisfied and 10 means completely satisfied.

Recurrence of contracture in the previously operated field [10] will be assessed only at 6 months and 12 months post surgery by MCP and PIP joint extension deficit.

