### Analysis strategies

All analyses will be conducted using an Intention-to-treat approach using all randomized participants. The primary endpoint is assumed to follow a Normal distribution. Mean scores between groups at follow-up will be analysed using a general linear model with baseline DASH scores as a covariate and hospital and type of surgery also added as independent factors (these are used to stratify the randomization).

Range of movement and satisfaction will be similarly analysed. However, as multiple digits are likely to be involved per person, a generalised estimating equation (with a Normal error term) will be used to adjust for intra-person correlations. The proportion of individuals with recurrent DD will be compared between groups and analysed using Fisher's Exact test. Subgroup analyses will be undertaken by adding an appropriate interaction term to the general linear model or general estimating equation. An interaction between group and severity and group and type of surgery will be considered, i.e. a subgroup analysis of severity and type of surgery. It is acknowledged that the statistical power of such analyses is likely to be low but as these are of secondary concern it would be inappropriate to consider a potentially very large sample size increase simply on account of these.

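### The stated 51 patients per group does not follow from 15 points, SD 22 and 90% power at any conventional significance level; the discrepancy is conservative

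*Protocol article*

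**What the plan says.** The Sample size section of the protocol article bases the trial's size on the DASH, "where a difference of 15 points is considered to be a clinically important difference", and "using a between-group standard deviation of 22 points". From these it concludes that "a total of 51 patients would be needed in each group for a power of 90" per cent. It then allows for 20% loss to follow-up and arrives at 128 randomized.

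The abstract (Methods/Design) carries the same 15 points and says that "a total of 51 patients will be needed in each group for a power of 90" per cent. It does not mention the SD.

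Neither place gives a significance level or says whether the test is one- or two-sided. Analysis strategies adds that "The primary endpoint is assumed to follow a Normal distribution" and plans a general linear model, so a comparison of two Normal means is the natural basis for checking the figure.

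**The concern.** A comparison of two means with a given difference, SD and power leaves only the significance level open. If no usual level turns 15, 22 and 90% into 51, at least one published figure is not the one that was used, or a step is unreported. The reader cannot tell which.

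This calculation is the article's only justification for the trial's size. Anyone judging what the trial could detect, or borrowing its assumptions for a later trial, would start from an inconsistent set of figures. The wording of the SD adds to the doubt. The calculation needs the spread of DASH scores among patients within a group, but the article calls 22 a between-group SD.

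**Working it through.** **Inputs.** Difference 15, SD 22, power 90%, 51 per group, 20% loss and 128 randomized all come from Sample size. Two equal groups follow from the same n in each and from Randomization. The significance level is not given. Two-sided 5% is assumed first, then varied.

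**1. Trying to reproduce 51.** Normal approximation:

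n per group = 2 × (z for alpha + z for power)² × SD² / difference² = 2 × (1.960 + 1.2816)² × 22² / 15² = 45.2, so 46.

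The t-test (noncentral t) gives 46.2, so 47. The stated figure is 51, which is 4 to 5 more per group.

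**2. Varying the unstated significance level**, at 90% power:

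| Two-sided alpha | Equivalent one-sided alpha | n, normal | n, t-test |
|---|---|---|---|
| 0.10 | 0.05 | 37 | 38 |
| 0.05 | 0.025 | 46 | 47 |
| 0.025 | – | 54 | 55 |
| 0.02 | 0.01 | 57 | 58 |
| 0.01 | – | 65 | 66 |

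None gives 51. Reaching 51 at 90% power would take a two-sided alpha of about 0.031 (normal) to 0.034 (t-test).

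**3. What else would give 51.**
- At two-sided 5% and 90% power: an SD of about 23 (by t-test, SD 23 gives exactly 51), or a difference of about 14.1 to 14.3 points.
- With 15 and 22 kept: about 92.5% power at two-sided 5% (t-test), or 80% power at two-sided 1% (normal).
- Inflating for a rank test (dividing by 0.955) gives about 48 to 50, still not 51, and the planned model is a Normal-theory one.

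Each route to 51 departs from a stated value or needs an unconventional alpha.

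**4. What 51 per group delivers** at two-sided 5% and SD 22. The standard error of the difference is 22 × √(2/51) = 4.36.
- Power for 15 points: 15 / 4.36 = 3.44; 3.44 − 1.96 = 1.48, giving 93.1% (normal). The t-test gives 92.6%.
- Difference detectable at 90% power: 3.2416 × 4.36 = 14.1 points (normal), or about 14.3 (t-test).

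**5. Allowance for loss.** 2 × 51 = 102, and 102 / 0.8 = 127.5, so 128. This step reproduces. From 47 per group it would give 94 / 0.8 = 117.5, so 118. From 46 it would give 92 / 0.8 = 115, or 116 for equal groups.

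**The case against.** The strongest reply is that a condensed article need not show everything. The significance level, or an extra inflation, may be in the full protocol. For example, 46 × 1.1 = 50.6 rounds up to 51. The figure may therefore be incompletely reported rather than miscalculated. That is fair as far as it goes: the 46 to 47 rests on an assumed alpha, and leaving alpha out of an article would not by itself be a finding. But nothing in the text mentions such an inflation, and supplying a conventional alpha does not make the published figures agree.

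It is also fair that the consequence is small. The promised 90% is exceeded, and no recruitment or analysis decision changes. The SD label has no numerical effect if 22 is in fact the within-group value.

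A reader might infer more than this, in three ways:
- **That the trial is underpowered.** On the stated inputs the reverse holds.
- **That sizing should have used the planned model with baseline DASH as a covariate.** Sizing on an unadjusted comparison is a common and conservative choice. Adjustment lowers the n required, so it cannot explain 51. The article gives no baseline-to-follow-up correlation from which to compute an adjusted figure.
- **That 15 points is too ambitious because Outcomes reports a responsiveness effect size of 0.5.** That figure describes change over time within patients, not a difference between splint and no splint, and its denominator is not given.

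**Conclusion.** The point stands as a reporting error in a headline figure. The article's 15 points, SD 22, 90% power and 51 per group cannot all be right under any conventional significance level. At an assumed two-sided 5% the excess is 4 to 5 per group (8 to 10 evaluable patients), and actual power for 15 points is about 93%.

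The direction is conservative, and the target of 128 follows correctly from 51 per group. The conclusion rests on equal groups, a Normal-theory comparison of means and 22 being the within-group SD. The size of the gap depends on the assumed alpha; the failure to reproduce 51 holds at every conventional level tried.

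**What to change.** Keep 128 randomized. In Sample size, state the significance level and sidedness, then do one of two things:
- if 15 points, SD 22 and two-sided 5% were intended, say that 51 evaluable patients per group give about 93% power;
- if other inputs produced 51, report those instead.

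Describe the 22 points as the within-group (between-patient) SD. Bring the abstract's power statement into line.

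The cost is a sentence or two in the Sample size section and one in the abstract. Recruitment and analysis do not change.

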### Analysis strategies

All analyses will be conducted using an Intention-to-treat approach using all randomized participants. The primary endpoint is assumed to follow a Normal distribution. Mean scores between groups at follow-up will be analysed using a general linear model with baseline DASH scores as a covariate and hospital and type of surgery also added as independent factors (these are used to stratify the randomization).

Range of movement and satisfaction will be similarly analysed. However, as multiple digits are likely to be involved per person, a generalised estimating equation (with a Normal error term) will be used to adjust for intra-person correlations. The proportion of individuals with recurrent DD will be compared between groups and analysed using Fisher's Exact test. Subgroup analyses will be undertaken by adding an appropriate interaction term to the general linear model or general estimating equation. An interaction between group and severity and group and type of surgery will be considered, i.e. a subgroup analysis of severity and type of surgery. It is acknowledged that the statistical power of such analyses is likely to be low but as these are of secondary concern it would be inappropriate to consider a potentially very large sample size increase simply on account of these.

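### Recurrence is tested with an unstratified Fisher's exact test although randomization and the DASH model use hospital and procedure; a stratified test would be a small, nearly free gain in efficiency and consistency

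*Protocol article*

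**What the plan says.** The Analysis strategies section of the protocol article fixes the test for recurrence: "The proportion of individuals with recurrent DD will be compared between groups and analysed using Fisher's Exact test". No stratum or covariate is attached to it.

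The Randomization section says: "Randomization will be stratified by recruiting hospital (5 centres) and surgical procedure (dermofasciectomy or fasciectomy) in block lengths of 4". Five hospitals and two procedures make ten strata.

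For the DASH, Analysis strategies specifies a general linear model with the baseline score, and "hospital and type of surgery also added as independent factors (these are used to stratify the randomization"). Range of movement and satisfaction are to be handled in like manner. Recurrence is therefore the one listed outcome whose stated analysis leaves out the design factors.

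The Outcomes section makes recurrence secondary and sets its timing: "Recurrence of contracture in the previously operated field [10] will be assessed only at 6 months and 12 months post surgery". The Sample size section is built on the DASH alone. The article states no expected recurrence rate, no significance level and no power for recurrence.

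**The concern.** The article's own reason for adjusting the DASH model, that hospital and procedure were used to stratify, applies equally to recurrence. Stratified allocation tends to balance these factors between arms. If they predict recurrence, an unstratified test then works with a variance that is too large and gives away power.

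Fisher's test adds a second loss. It conditions on both margins, so its attainable significance levels are discrete and its true size lies below the nominal level at this sample size.

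The Background reports splinting as both increasing and delaying recurrence, so the direction is open. The trial was not sized for this outcome, so power that can be kept at no cost is worth keeping.

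**Working it through.** **Inputs.** The article gives "a total of 51 patients would be needed in each group for a power of 90"% and "Allowing for a 20% loss to follow-up a total of 128 patients need to be randomized". The dropout step reproduces: 102 / 0.8 = 127.5, so 128; and 128 × 0.8 = 102.4, or about 51 evaluable per arm. The 51 itself is taken as stated. With 15 points, SD 22, 90% power and an assumed two-sided 5% level, 2 × (1.960 + 1.282)² × (22/15)² = 45.2, so 46 per arm. That difference does not bear on this point. There is no stated figure for recurrence to reproduce. I assume a two-sided 5% level and vary the recurrence rate.

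**Step 1: true size of Fisher's test.** For a common recurrence rate p, add up the probabilities of all tables that Fisher's test rejects:

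size(p) = Σₓ Σᵧ b(x; 51, p) · b(y; 51, p) · 1[P_Fisher(x, y) ≤ 0.05]

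| Assumed recurrence | 5% | 10% | 15% | 20% | 30% | 40% | 50% |
|---|---|---|---|---|---|---|---|
| True size, 51 per arm | 0.0075 | 0.0183 | 0.0245 | 0.0288 | 0.0313 | 0.0337 | 0.0371 |
| True size, 64 per arm | 0.0118 | 0.0233 | 0.0279 | 0.0297 | 0.0308 | 0.0354 | 0.0298 |

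The test stays below 5% throughout. The shortfall is large at about 10% recurrence or less and moderate above that.

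**Step 2: stratified alternative.** In stratum k, let X be the events in the splint arm, S the events in both arms, n₁ and n₀ the arm sizes, and N = n₁ + n₀. The Cochran-Mantel-Haenszel (CMH) statistic without continuity correction is

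z = Σ(X − S·n₁/N) / √Σ[n₁·n₀·S·(N − S) / (N²(N − 1))]

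Simulation: ten strata with 9, 5, 6, 5, 6, 4, 5, 4, 4 and 3 patients per arm (51 in total), 20,000 runs. Stratum risks vary on the logit scale with the SD shown.

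| Logit SD between strata | Null rejection, Fisher / CMH | Alternative rates | Power, Fisher / unstratified chi-square / CMH |
|---|---|---|---|
| 0 | 0.028 / 0.046 | 20.0% vs 40.5% | 0.550 / 0.626 / 0.622 |
| 0.5 | 0.025 / 0.048 | 21.5% vs 41.8% | 0.525 / 0.606 / 0.617 |
| 1.0 | 0.021 / 0.048 | 26.9% vs 45.9% | 0.427 / 0.517 / 0.583 |
| 1.5 | 0.015 / 0.051 | 28.5% vs 45.6% | 0.340 / 0.432 / 0.545 |

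With no spread between strata, the gain is 0.622 − 0.550 = 7 points. All of it comes from leaving Fisher's conservatism, since chi-square gains as much. At a logit SD of 1, the gain is 0.583 − 0.427 = 16 points: 0.517 − 0.427 = 9 from the conservatism and 0.583 − 0.517 = 7 from the stratification. The article supports no particular spread, so the lower rows only show direction.

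A further simulation with ten strata and 102 evaluable patients, extended down to 5% to 10% recurrence, gave CMH null rejection of 0.042 to 0.056 and gains of about 5 to 11 points. I use that as the headline range.

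**Step 3: rare events.** At 5% and 10% recurrence, 102 patients give about 5.1 and 10.2 events. A logistic model with treatment (1 term), hospital (4) and procedure (1) has six terms, so 5.1 / 6 = 0.85 and 10.2 / 6 = 1.7 events per term. With five equal hospitals of 20.4 patients, the chance that at least one has no event is 1 − (1 − 0.95^20.4)^5 ≈ 0.88 at 5% and 1 − (1 − 0.90^20.4)^5 ≈ 0.46 at 10%. That hospital's coefficient then has no finite maximum-likelihood estimate. CMH does not break down; it only drops strata that carry no information.

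**The case against.** The other side has a good case, and much of it stands.

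- **Validity.** Fisher's test keeps the type I error at or below nominal, and leaving out the strata errs in the same safe direction. A reader might infer that the planned test is wrong or that a positive result could not be trusted. Neither follows.
- **Degree of conservatism.** A reader might call the test strongly conservative at this size without qualification. That depends on a recurrence rate the article does not give. It fits rates of about 10% or below, but at 15% to 50% the loss is moderate. The intention-to-treat statement covers all randomized patients; with 64 per arm the size at 5% and 10% rises to 0.012 and 0.023.
- **Effect estimate.** One could read the sentence as promising a p-value and nothing more. Naming a test does not exclude an estimate with an interval, and such detail is commonly left to an analysis plan, which is not shown here.
- **Prognostic strength.** The article considers type of surgery for a subgroup interaction but gives no data linking it or hospital to recurrence. The part of the gain that comes from stratification is therefore unproven.
- **Sparse strata.** Ten strata average about ten patients each, and those without events or with only one arm contribute nothing. This objection defeats the six-term logistic model as an equivalent choice when events are rare. It does not defeat CMH, which held its size at 5% to 10% recurrence.

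What remains is that the article states a particular test, that this test departs from the article's own reason for adjustment, and that a better one is available from data already collected.

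**Conclusion.** The point holds as a minor matter of efficiency and consistency on a secondary outcome. It does not touch the primary result and does not make the recurrence analysis invalid. The likely benefit of changing is about 5 to 11 points of power at a size of roughly 5%, and more only if strata differ strongly in risk.

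This rests on a two-sided 5% level, about 51 evaluable patients per arm, assumed recurrence rates, and, for the tabulated simulation, arms of equal size within strata. Loss to follow-up and incomplete blocks would disturb that balance somewhat.

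Nor should a reader infer that the change would make a non-significant result conclusive. For 20% against 40% recurrence, power stays near 60% with either unstratified chi-square (0.607) or CMH (about 0.62).

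**What to change.** Replace the recurrence sentence in Analysis strategies with one that says:

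- The proportion with recurrence at 12 months is compared by a CMH test stratified by hospital and procedure, without continuity correction (the correction would give back much of the gain). The 6-month comparison is supportive.
- The stratified risk difference is reported with its 95% confidence interval.
- Sparse strata are pooled by a rule set in advance, for example stratifying by procedure only. Fisher's test is the fallback if events are very few, with the threshold stated.

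Logistic regression with hospital and procedure should not be listed as interchangeable, because it may fail when events are rare.

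The cost is a few lines of text. No new data or visits and no change in sample size are needed. The small downside is that uninformative strata drop out, which the pooling rule limits.

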## Discussion

This pragmatic randomised controlled trial will provide much needed evidence on the clinical effectiveness of post-operative night splinting in patients who have undergone fasciectomy or dermofasciectomy for DC.
